### Safety, Data Management, and Confidentiality

During the trial, all patient data will be kept in a secure room accessible only by the research group. All data will be deidentified and treated according to the standards set by the Norwegian Data Inspectorate (Datatilsynet), in compliance with the Health Research Act and the Personal Data Act.

## Results

Data collection was completed in August 2019. In total, 39 patients admitted at 3 treatment centers participated in the study. Data will be analyzed during 2020.

## Discussion

Many SUD clinics have begun to implement physical activity as part of routine inpatient treatment due to its reported benefits. This study on acute exercise will add clinically relevant information about the short-term effects of soccer and circuit training on mood, craving, state anxiety, and self-esteem in this population. Most previous studies have performed pre-exercise and postexercise assessments only. The current study will add information on how the effects develop beyond the immediate cessation of exercise. The activities in the study are readily available, inexpensive, and popular in the general population. If the interventions are effective, they can easily be integrated into different clinical settings, for both inpatients and outpatients, and adapted to the participant’s fitness level.

The study is designed to reflect the clinical realities of inpatient treatment for SUDs. Typically, patients use multiple substances [3,35]. The inclusion of patients with comorbid SUD and mental disorders will give the study a high ecological validity but might also make the results difficult to interpret. Different drugs and various mental disorders might be affected in different ways by the interventions. Gathering information on the participants’ co-occurring disorders will potentially enable subgroup analyses to differentiate exercise effects in those with different combinations of substance and mental health problems.

Craving is highly relevant in clinical settings, even though the nature of it and the items included in instruments that assess craving have been debated [15,46,47]. By using a single-item scale, it will not be possible to capture changes in different aspects of craving. The participants might have different perceptions of craving, varying from a subjective desire to consume a substance to various bodily sensations. This is a potential limitation. However, previous studies assessing acute craving have used single-item VAS scales [48,49]. As the aim of the present study is to assess changes in participants’ overall subjective experience of craving and whether exercise can help attenuate it, we believe that a single-item scale can adequately capture this.

Using saliva samples is a noninvasive method for assessing cortisol levels. There is no need for medical staff, and saliva can be stored at room temperature for several hours before freezing. The drawback of saliva cortisol (versus serum cortisol) is that the use of tobacco and the presence of blood in the samples may lead to falsely elevated cortisol levels [50]. To control for this, the laboratory will not analyze samples with traces of blood. Samples with cortisol levels above reference levels will be excluded from analysis.

Dropout rates from treatment studies of SUDs are often high [6,28]. To minimize the risk of dropout, a member of the research group visited the treatment center 1 week before the study to answer questions. The recruitment took place a maximum of two weeks ahead of the trial. We tried to minimize dropout by keeping the overall intervention period short and integrating the interventions into the usual treatment routines at the treatment centers. This also minimized interference in the patients’ usual treatment.

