## Introduction

Substance use disorders (SUD) have wide-reaching impacts on health and well-being and contribute substantially to the global disease burden [1]. They are associated with shorter life expectancy, and comorbid medical conditions are common [2]. The prevalence of co-occurring personality and other psychiatric disorders is high, with estimates ranging from 50% to 90% [3]. Mood and anxiety disorders are prevalent and affect both the severity and outcome of treatment [4]. Current treatment options for SUDs include cognitive behavioral therapy, motivational interviewing, and medication. Although documented as effective, these methods do not help all patients. Relapse rates range between 40% and 60% [5], and dropout rates from in-patient treatment is around 30% [6].

Despite their high prevalence, few people with SUDs ever receive treatment, and there is a need for more treatment options [7,8]. One potential explanation for poor help seeking is the perceived stigma associated with traditional treatments [9,10]. Lifestyle-focused interventions have potential to increase help seeking by reducing this stigma.

Physical activity has been suggested as an alternative or complementary treatment option for SUDs [11-13]. The rationale is that physical exercise might be effective due to its beneficial effects on factors related to relapse and the maintenance of the disorder, such as comorbid mental disorders, craving, and emotional dysregulation [14-17].

Regular physical activity increases fitness and lowers the probability of chronic diseases [18,19]. It has been proposed as a strategy for alleviating symptoms of psychiatric disorders in general [20,21], and its application in the mental health care system is increasing. Regular physical activity has been shown to be effective in the prevention and treatment of common mental health conditions [22]. Studies also indicate that physical activity alleviates symptoms in people suffering from severe mental disorders [23]. Acute bouts of exercise have cognitive and mood-enhancing benefits, including improved executive functioning and lower state anxiety and stress reactivity [24,25]. The mechanisms behind the psychological benefits of exercise in SUDs are not well established, but one tenable hypothesis is that they are partly mediated by changes in the stress hormone cortisol [24].

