The misuse of a single substance is exceptional in SUDs [35]. Whether acute exercise can benefit people with polysubstance dependencies is unclear. Most studies have assessed aerobic forms of exercise, often in laboratory conditions using stationary bicycles [12,28]; little is known about other forms of exercise in clinical settings. With some exceptions [25], psychological benefits across different forms of exercise have not been compared, and it is unclear how long the changes last following a single exercise session. Studies have mostly used pre- and postassessments only, which is a limitation.

To address these questions, we conducted a feasibility study to compare the short-term effects of 3 different exercises (soccer, circuit training, and walking) conducted in nonlaboratory settings [36]. Findings suggested that moderately intense exercise activities performed in natural settings may increase mood, help attenuate drug cravings, increase positive affect, decrease negative affect, and improve self-esteem. The results were promising but need to be replicated with a larger sample and a randomized design.

In this study, we are conducting a multicenter randomized controlled trial to compare the short-term effects of 2 forms of exercise (soccer and circuit training) with a control condition (a lecture on the health benefits of physical activity) in polydrug-dependent inpatients. We chose to compare the effects of exercise to a nonexercising control group (lecture) instead of a walking-based intervention, as previous studies have shown that even light physical activity can have mood-enhancing effects [37]. We are also performing biomarker analyses of cortisol to better understand the underlying mechanisms.

Key research questions that will be addressed include (1) What are the short-term effects of soccer and circuit training on mood (primary outcome), drug craving, positive and negative affect, state anxiety, and self-esteem in adults with SUD? (2) How long do the effects last after the exercise sessions end? (3) Are there differences between the two forms of exercise? (4) Do the effects differ with the intensity of the exercise? and (5) Are the study outcomes associated with changes in the stress hormone cortisol?

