#### Biomarkers

Cortisol level was measured immediately before and 4 hours after the interventions. Saliva samples were collected using cotton swabs (Salivette; Sarstedt Inc). Collected samples were stored in a freezer until the end of the study. The cortisol level in saliva will be measured by liquid chromatographic–tandem mass spectrometry. The analyses will be performed at the Hormone Laboratory at Oslo University Hospital.

Consistent with Salivette recommendations, participants were asked not to eat or drink, use tobacco, or brush their teeth 60 minutes before the saliva samples were taken.

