### Statistical Analyses and Power Calculation

Statistical power was estimated using G*Power (version 3.1.9.7; Heinrich-Heine-Universität Düsseldorf). Parameters were based on results from our feasibility study [36] and also took into account previous studies demonstrating medium effect sizes for acute exercise on mood states [38,45]. Assuming an effect size of 0.3 and power (β) of .8, with 3 groups and 5 measurement points, we estimate needing at least 21 participants to test our hypotheses. We planned to include one group of 5 to 10 participants from each site, which would give us 20 to 40 participants. Due to the experimental study design and the inclusion of only inpatients, we anticipate minimal missing data. Descriptive data will be calculated for each measure. Changes over time will be assessed using mixed (group × time) repeated-measures analysis of variance with post hoc contrasts. If participants return questionnaires with missing data, the missing items will be imputed using the last observation carried forward method. If questionnaires are returned with more than 50% of data missing, the questionnaire will be excluded from the analysis.

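### Cortisol samples are dropped solely because the value is above reference, which is expected to attenuate condition differences in cortisol by an amount the article does not let one fix

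*Protocol article*

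**What the plan says.** Research question 5 in the Introduction asks: "Are the study outcomes associated with changes in the stress hormone cortisol". The Introduction also puts forward, as a possible mechanism for the psychological benefits of exercise, that "they are partly mediated by changes in the stress hormone cortisol". Under Biomarkers, "Cortisol level was measured immediately before and 4 hours after the interventions". With three conditions that makes six samples per participant.

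The Discussion gives the reason for screening samples: "the use of tobacco and the presence of blood in the samples may lead to falsely elevated cortisol levels". Two rules follow. First, "the laboratory will not analyze samples with traces of blood". Second, "Samples with cortisol levels above reference levels will be excluded from analysis". For tobacco there is also a precaution before sampling, under Biomarkers: "participants were asked not to eat or drink, use tobacco, or brush their teeth 60 minutes before the saliva samples were taken".

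The article states no reference limit, no expected share of samples above it, and no analysis that keeps the high values in.

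**The concern.** The second rule needs no sign of contamination; a high result is enough. It therefore removes true high values together with false ones, and it does so for a variable that the trial set out to study. The exclusion happens after randomisation and depends on the outcome. If one condition raises cortisol, more of that condition's 4-hour samples cross the limit and are deleted, and those deleted are the ones that carry the effect. If a condition lowers cortisol, the comparator loses more of its high values. Either way the retained means are normally drawn together. Each deletion, before or after the session, also removes a change score, and change is what question 5 is about.

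At stake is the reading of a small or null cortisol difference between exercise and lecture: it could not be told apart from the work of the exclusion rule.

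**Working it through.** **Plan's own figure.** The article gives no number for cortisol. Its one computed figure is the minimum of 21 participants, from "Assuming an effect size of 0.3 and power (β) of .8, with 3 groups and 5 measurement points". With assumed alpha 0.05, correlation 0.5 and no sphericity correction, the interaction test has λ = 0.3² × N × 5 / (1 − 0.5), with 8 and 4(N − 3) degrees of freedom. Power is 0.806 at N = 19 and 0.856 at N = 21, the next multiple of three groups. So 21 reproduces, and no cortisol quantity enters it.

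**Inputs assumed, because the article gives none.** Log cortisol at 4 hours is normal with SD 1 in each condition; the lecture mean is 0 and the exercise mean is d; a share p of lecture samples lies above the limit c, so c = Φ⁻¹(1 − p); all high values are genuine.

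**Step 1: difference in 4-hour level.** The mean of a normal variable cut from above is μ − φ(c − μ)/Φ(c − μ). The observed difference is therefore [d − φ(c − d)/Φ(c − d)] + φ(c)/Φ(c).

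Example with p = 2.5% (c = 1.96) and d = 0.5: the exercise mean is 0.352 and the lecture mean −0.060, so the difference is 0.352 + 0.060 = 0.412. The share deleted under exercise is 1 − Φ(1.46) = 7.2%, against 2.5% under lecture.

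| Lecture samples above limit | Rise of 0.5 SD seen as | Exercise samples deleted (rise) | Fall of 0.5 SD seen as |
|---|---|---|---|
| 2.5% | 0.41 | 7.2% | 0.46 |
| 5% | 0.37 | 12.6% | 0.43 |
| 10% | 0.32 | 22% | 0.39 |
| 20% | 0.26 | 37% | 0.33 |

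For rises of 0.3 to 0.8 SD the shrinkage is 15-22% at p = 2.5% and 33-41% at p = 10%. For falls of the same size it is 6-10% and 19-25%.

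**Step 2: difference in pre-to-4-hour change.** By simulation, with both samples cut at the limit, p from 2.5% to 20% and pre-post correlation 0.3 to 0.6, the difference in change keeps 63-92% of a true 0.5 SD rise and 75-97% of a true fall. At p = 5% and correlation 0.5, 0.50 becomes 0.43 for a rise and 0.46 for a fall.

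**Step 3: association asked for in question 5.** A true correlation of 0.30 between cortisol change and an outcome becomes 0.292, 0.286, 0.278 and 0.263 at p = 2.5%, 5%, 10% and 20%.

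**Step 4: lost data.** If each of six samples exceeds the limit independently with probability p, the share of participants who lose at least one is 1 − (1 − p)⁶: 14%, 26% and 47% at 2.5%, 5% and 10%. Of the 39 participants, about 33, 29 and 21 would have all six. For a given p this overstates the loss, since one person's samples are correlated.

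**Step 5: patterns that behave differently** (p = 5%, correlation 0.5). If only pre-session samples exceed the limit and the effect is uniform, 0.50 stays 0.50. If exercise lowers cortisol only in those with low pre-session values, −0.50 becomes −0.53. If a rise is confined to 30% of participants, a mean effect of 0.50 falls to 0.24.

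**The case against.** The best defence is that the rule has a purpose that nothing else in the article serves. Two sources of false elevation are named. The laboratory's rule deals with blood; for tobacco there are only requests made to participants beforehand. The above-reference rule is thus the sole check on tobacco after collection, and not every value it removes need be genuine. Under assumed contamination (10% of samples raised by 3 SD), deletion still lowers the raw difference (0.50 to about 0.42), but the standardised effect is better than with everything kept (about 0.42 against 0.31). If contamination differs by condition, deletion can also come nearer the truth: with 20% of samples contaminated in general but 10% of 4-hour exercise samples, a true 0.50 is seen as 0.20 with all samples kept and 0.39 with the cut. This stands. It argues for screening on evidence of contamination and for showing both analyses; it does not justify a cut on the value as the only analysis.

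A reader might infer that the rule shrinks any exercise effect on cortisol. It does not: the patterns in the last step of the working show no bias, or a slight exaggeration. A reader might also infer that question 5 is pushed to a null answer. That question concerns an association, and a fall from 0.30 to 0.29-0.26 does not support so strong a claim. The condition difference and the lost samples are where the damage would lie.

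Finally, a fuller plan might state the limit and whether it is specific to time of day. That bears on the size of the effect, not on the rule as published.

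**Conclusion.** The point holds in a limited form. The article fixes an unconditional exclusion on the measured value of a variable under study. The rule is expected to attenuate condition differences in cortisol, to delete samples unequally by condition if condition affects cortisol, and to cost change scores.

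The principle is secure; the magnitude is not. The range of 0.41 to 0.32 SD for a 0.5 SD rise, and 0.46 to 0.39 SD for a 0.5 SD fall, rests on normal log cortisol, a uniform shift, no contamination and an assumed 2.5% to 10% of lecture samples above the limit. If no sample exceeds the limit, the effect is nil.

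Cortisol is a mechanistic question, the last of five. The Feeling Scale result, the other self-report outcomes and the figure of 21 participants are unaffected. The change is worth making, but it does not threaten the trial's main conclusion.

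**What to change.** Replace the above-reference rule for the main cortisol analysis. Use every sample the laboratory can assay, on the log scale. Exclude a sample only on evidence of contamination that does not depend on its value, judged blind to condition: visible blood, and a breach of the 60-minute rule if breaches were recorded. The article says only that participants were asked to comply, so the second criterion may not be available; visible blood, the log scale and the sensitivity analysis would then carry the remedy.

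Report the above-reference exclusion as a sensitivity analysis, state the limit used, and give the number of samples excluded for each condition and time point.

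The cost is a sentence or two of text and one further analysis, with no new data. The article describes the assays and the analysis as still to come, so at publication the change could have been made before results were seen. The downside is that some tobacco-contaminated high values may stay in the main analysis and add noise; the log scale and the sensitivity analysis limit this.

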## Abbreviations

CONSORT: Consolidated Standards of Reporting Trials
ICD-10: International Classification of Disease, Tenth Revision
PANAS: Positive and Negative Affect Schedule
RPE: Rating of Perceived Exertion
SPIRIT: Standard Protocol Items: Recommendations for Interventional Trials
SUD: substance use disorder
VAS: visual analog scale
